### Qualitative evaluation

Semi-structured interviews will be conducted with a subsample of Group PM+ participants (equal number of completers and non-completers); Group PM+ facilitators; control arm participants; research assistants; family members of Group PM+ participants (equal number of intervention completers and non-completers); community informants; and local decision makers. The interviews will be conducted by trained interviewers that are familiar with the key principles of qualitative interviewing. Interviews will follow a semi-structured topic guide that address themes around barriers and facilitators in implementing PM+, satisfaction with the intervention, barriers and facilitators to adherence, and barriers and facilitators to scale up and integrating Group PM+ into other services.

All interviews will follow the same process: Group PM+ participants and other Key Informants (KIs) will be selected through convenience sampling. Informed consent will be obtained using a single step procedure where participants are provided oral and written information about the study and its purpose in the local language. The number of KI interviews in each category of respondent will be determined by empirical saturation, with a minimum of 2–16 participants per each category. FGDs will also be conducted in relevant categories.

#### Qualitative data analyses

The qualitative data collected from FGDs, key informant interviews, and notes during the process evaluation will be coded in NVIVO [60] and analyzed using content analysis [61] on the translated transcripts of the original language. Coding will be conducted by multiple independent raters, and inter-rater reliability will be calculated using Kappa scores.

### Ethical considerations

Throughout the different study phases participants in both arms will have access to mhGAP-trained health staff in the districts. When necessary they will be referred to a specialist for further assessment or management of severe psychiatric problems. If a participant experiences psychological problems after the project, they will be offered additional support.

All adverse events (AEs) and serious adverse events (SAEs) that are reported spontaneously by the participant or observed by either research or intervention staff will be recorded. All staff will be trained in the TPO Nepal Adverse Events Reporting Mechanism, which guides the process of reporting and supporting/referral in case of any adverse events.

All AEs and SAEs will be reported to a local independent Data Safety Management Committee (DSMC). The DSMC includes psychiatrists, non-governmental organization experts in psychosocial programs, and researchers and is established specifically for oversight of the trial and review of SEs and SAEs. The chair or a nominated person from the DSMC will review SAEs within 48 h, deciding if an SAE is likely related or unrelated to the intervention. The DSMC will review all AEs once a month. In both instances the committee will, where necessary, determine any appropriate action in respect of ongoing trial conduct (i.e., referral to specialized care). All changes in treatment resulting from AEs or SAEs will be reported to the DSMC in Nepal. TPO Nepal is responsible for data collection and storage and making data available to the DSMC, funders, and IRBs for audits when appropriate.

The project has been approved locally by the Nepal Health Research Council, Kathmandu, Nepal and by the WHO Ethical Review Committee (version 3; protocol ID 2817, October 25, 2018).

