### Study arms

#### Group PM+ intervention

Problem Management Plus (PM+) is a WHO trans-diagnostic psychological intervention that is delivered by trained non-specialist lay-providers in five sessions to adults impaired by distress [1, 2]. The manual comprises of the following evidence-based techniques: (a) problem solving, (b) stress management, (c) behavioral activation, and (d) accessing social support.

The Group PM+ intervention consists of five 2.5- to 3-h sessions in which participants are taught techniques to manage their stressors and problems. Table 1 gives an overview of the content of the five sessions. The aim is to have six to eight participants per group, with separate groups for men and women and with gender-matched facilitators. Information on seeking services from local health facilities with mhGAP-trained health care staff trained in providing mental health care and/or psychosocial support is provided to the Group PM+ participants as well as to the EUC participants.

**Table 1 Tab1:** Mechanisms of action of PM+ intervention

PM+ mechanisms of action	Description of mechanism	Implementation of mechanism
*Stress management*	Participants learn deep breathing. They are encouraged to incorporate this mechanism into daily life (i.e., when doing housework, walking, etc.). Grounding techniques are incorporated to bring participants back to the present	Session 1
*Behavioral activation*	Participants review the inactivity cycle. They choose a small activity that they enjoy doing (i.e., making and drinking tea, meeting a friend etc.) and create a detailed plan about when and how to conduct this activity as a first step in breaking the inactivity cycle	Session 2
*Managing problems*	Participants learn which of their problems are solvable and which are unsolvable. One problem is chosen amongst the solvable problems and participants brainstorm tangible solutions, then create manageable steps to accomplish their goals	Session 3
*Strengthening social support*	Participants learn to recognize who amongst their family and friends are existing and potential sources of support and how best to strengthen connections with them. Social network mapping activities are incorporated into this mechanism	Session 4

The first four sessions of PM+ each addresses a specific mechanism of action. The fifth and last session is a review of the mechanisms of actions learned in the previous sessions

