Three types of supervision will be provided by TPO Nepal supervisors for PM+ providers while running the PM_ groups. Firstly, face-to face group supervision will be provided in the office twice a week for Group PM+ facilitators. Secondly, there is on-site supervision, in which a supervisor will sit in and observe at least two sessions per PM+ group. Fidelity and competency assessments will be conducted during these sessions to verify the delivery of Group PM+ to participants. Intervention fidelity is monitored through independent observations of 10–15% of sessions of each facilitator against tailored checklists. Fidelity and competency tools will be used and direct feedback will be given to PM+ facilitators leading the group. These sessions will also be audio recorded and reviewed in the in-office supervision sessions. Lastly, individual supervision sessions between the supervisors and Group PM+ facilitators will be conducted as needed. Supervision sessions will be documented using standard supervision forms and facilitators will discuss any reoccurring or unique challenges and successes during the sessions with the supervisors.

Facilitators are supported by assistants called “Group PM+ helpers” who receive a basic 1-day training on assisting Group PM+ delivery and participate alongside CPSWs in practice PM+ groups. They help with the logistics and organizational aspects of the group sessions, such as reminding participants when sessions take place, reminding those that do not show up for the sessions, and providing child care. Additional tools such as calendars, session cards, and reminders, all developed specifically for the Nepal implementation of Group PM+, are used to increase retention of the material and attrition by participants.

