#### Enhanced usual care

In rural regions of Nepal, care-as-usual for most people with mental health problems until recently consisted of no psychological or psychiatric treatment in local health facilities. People with severe mental conditions would often, after a long delay between onset of symptoms, be taken to tertiary psychiatric services in the Kathmandu valley, or other urban settings with psychiatric services, by family members [21]. The Programme for Improving Mental Health Care (PRIME) has been implemented in Chitwan district, in southern Nepal, and has implemented and evaluated the WHO mental health Gap Action Programme (mhGAP) Intervention Guide since 2012 [22, 23]. The mhGAP *Humanitarian* Intervention Guide [24] was contextualized for Nepal after the 2015 earthquakes and Nepali primary care workers in many districts, including Morang, have since been trained using mhGAP. Both the EUC and intervention arm will receive a referral to a mhGAP trained primary health care worker providing treatment when needed (e.g., severe psychiatric disorder or suicidality) .

Participants in the EUC control clusters will receive a time-restricted (between 30 and 45 min) family meeting conducted by local Community Informants (CIs) that will consist of: (a) basic information on adversity and mental health, (b) benefits of getting support, (c) information on seeking services from local health facilities with mhGAP-trained health care staff trained in providing mental health care and/or psychosocial support [10]. The mhGAP training that these health care staff received consists of a 6-day training, focusing on a selected number of mental disorders including common mental disorders, including an additional module on anxiety disorders (excluding PTSD). This family meeting will be conducted with family members of the participant or the participant only based on participants’ preferences. Both arms will receive the same family meeting format and referral information to primary care-based treatment.

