### Procedures

Each ward of participating municipalities in Morang district will have one community informant (CI) who will conduct recruitment through the use of the Community Informant Detection Tool (CIDT) and community sensitization activities. CIs are often Female Community Health Volunteers (FCHVs), mothers’ group members, or social mobilizers within their respective communities. CIs will, as much as possible, also be gender-matched for the “gender” of their wards. CIs from intervention and control wards will be trained separately to maintain blinding. Control ward CIs will not be given any information on Group PM+ or any other information about the existence of an intervention arm. Intervention CIs will additionally be given a 1-day training to become Group PM+ ‘helpers’ for the sessions.

The CIs will be trained on the CIDT to identity people with common mental disorders in the community. The CIDT is a pro-active case detection approach aimed to increase help seeking using a vignette-based tool designed for the ease of use by lay people. It has been developed and tested in Nepal [35], with positive results on the positive predictive value (0.68) and increasing the utilization of mental health services [36]. A general distress CIDT version had been adapted for this trial [28], which includes gender-matched vignettes for the “gender” of the wards.

After the community informant identifies a person in the community who matches the symptoms described in the vignettes, they will be asked if they would like support for their problems. If so, the research assistant (RA) will then conduct the consent and screening procedures.

People who are identified as meeting the exclusion criteria initially by the RAs will be referred to health workers trained in mhGAP, hospitals with psychiatric services, or counselors. People that meet the inclusion criteria for the study, in both the intervention and control wards, will receive a visit from the CI for a family meeting. Based on the preference of the participants, this can either be with or without their family. After the family meeting, RAs will conduct the baseline assessment with enrolled participants. Once baseline is completed, only those in the intervention group will be contacted by CPSWs to inform them about Group PM+. After all participants in an intervention ward have been contacted by the CPSW, Group PM+ sessions will start.

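### Adverse events are captured passively while only Group PM+ participants have scheduled staff contact between baseline and midline, so by-arm event counts are open to differential detection

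*Protocol article*

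**What the plan says.** **How events are captured.** Ethical considerations states that adverse events and serious adverse events "reported spontaneously by the participant or observed by either research or intervention staff will be recorded". Intervention staff are thus a named source. The same section adds: "All staff will be trained in the TPO Nepal Adverse Events Reporting Mechanism, which guides the process of reporting and supporting/referral". Events go to the safety committee, which reviews serious events within 48 hours, judges whether they are related to the intervention, and reviews all events monthly.

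**Contact in the Group PM+ arm.** After baseline, "only those in the intervention group will be contacted by CPSWs" (Procedures). Then, under Group PM+ intervention, "The Group PM+ intervention consists of five 2.5- to 3-h sessions", with a facilitator and a helper. During delivery "a supervisor will sit in and observe at least two sessions per PM+ group". Other measures and further data schedules the Subjective Units of Distress Scale for every participant at sessions two to five.

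**Contact in the EUC arm.** "Participants in the EUC control clusters will receive a time-restricted" family meeting of 30 to 45 minutes (Enhanced usual care). Both arms receive it, and Procedures places it before the baseline assessment.

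**Shared contacts.** Both arms are interviewed at midline (week 7) and endline (week 20) by assessors who are meant to be blinded. Table 2 lists no adverse-event question at either interview and marks suicidality at enrolment only.

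**The concern.** A passive rule records an event only if someone is there to hear of it or see it. Here one source, intervention staff, has scheduled contact after baseline in one arm only. With identical true event rates, following the rule as written gives PM+ events more chances to be recorded than EUC events.

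The population makes this matter. Under Participants, people with current suicidal ideation and plans or recent attempts are referred but not excluded, so serious events are foreseeable in both arms. The safety committee judges relatedness and may act on trial conduct, and a fair background rate from EUC is what would help it interpret events in PM+. If EUC events are recorded less completely, a harmless intervention could look worse than control and harm in the control arm could go unseen. The primary outcome is not affected.

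**Working it through.** The article gives no adverse-event rate or safety-comparison figure, so there is no plan figure to reproduce on this point.

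**Step 1. Scheduled contacts after baseline.**

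| Contact | PM+ | EUC |
|---|---|---|
| Facilitator contact after baseline (Procedures) | 1 | 0 |
| Group sessions (Group PM+ intervention) | 5 | 0 |
| Midline and endline interviews (Design and setting) | 2 | 2 |
| Total | 8 | 2 |

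Session time is 5 x 2.5 = 12.5 h to 5 x 3 = 15 h in PM+ and 0 h in EUC. The family meeting is left out because it is common to both arms and precedes baseline. The whole imbalance falls before midline; afterwards each arm has one scheduled contact, endline.

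**Step 2. What that could do to counts.** Assumptions, none given in the documents:
- each contact after onset reveals an event with probability q;
- true risk is equal in the two arms;
- onset is uniform over 20 weeks;
- sessions fall at weeks 2, 3, 4, 5 and 6 (midline is about a week after the last session), and all are attended;
- the facilitator contact is ignored, so PM+ has 7 contacts.

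An event with k contacts still to come is recorded with probability 1 - (1 - q)^k.

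- PM+: k = 7 for onset in weeks 0-2 (weight 2/20); k = 6, 5, 4, 3, 2 for onset in each of the next five weeks (weight 1/20 each); k = 1 for weeks 7-20 (weight 13/20).
- EUC: k = 2 for weeks 0-7 (weight 7/20); k = 1 for weeks 7-20 (weight 13/20).

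For q = 0.1:
- PM+: 0.10 x 0.522 + 0.05 x (0.469 + 0.410 + 0.344 + 0.271 + 0.190) + 0.65 x 0.100 = 0.052 + 0.084 + 0.065 = 0.201.
- EUC: 0.35 x 0.190 + 0.65 x 0.100 = 0.132.
- Ratio: 1.53.

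| q | PM+ recorded | EUC recorded | Ratio |
|---|---|---|---|
| 0.1 | 20.1% | 13.2% | 1.53 |
| 0.2 | 35.2% | 25.6% | 1.37 |
| 0.3 | 46.9% | 37.4% | 1.26 |
| 0.5 | 65.0% | 58.8% | 1.11 |
| 0.7 | 79.9% | 77.4% | 1.03 |

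In every row PM+ shows more recorded events although the true risks are equal.

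**Step 3. After the fix.** Counting only events asked about at midline and endline, the opportunities are 2 against 2, a ratio of 1.0.

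**The case against.** **No between-arm safety analysis is planned.** Adverse events are absent from the objectives, outcomes and statistical analyses. They appear only under Ethical considerations, for oversight and referral, where recording whatever staff notice is appropriate. This stands. A reader might infer that a planned safety comparison is invalid, or that the trial cannot speak to safety at all; the article supports neither. What remains is that counts reviewed or reported by arm carry the imbalance.

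**Some questions are symmetric.** The Traumatic Events Inventory is asked in both arms at baseline and endline, and symptom scales are asked in both at midline and endline. This is right, but the Inventory covers lifetime exposure and nothing links these instruments to adverse-event recording.

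**A larger ratio would be overstated.** If every event were present at all seven PM+ contacts and both EUC contacts, q = 0.1 would give 0.522/0.190 = 2.7 and q = 0.2 would give 0.790/0.360 = 2.2. That cannot be typical: 13 of the 20 weeks (65%) lie after midline, where the arms have equal scheduled contact. Incomplete attendance, which the analysis plan anticipates, lowers the ratio further, and an event such as a hospital admission may well have q above 0.2.

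**Detail may sit elsewhere.** The named reporting mechanism is not shown and could contain prompts. That tempers certainty, but the article describes it as guiding reporting and referral, and the capture rule it does state is passive.

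**Conclusion.** The point holds as a risk to any by-arm reading of adverse-event counts. It follows from the stated capture rule and contact schedule, not from detail the article leaves out. The expected direction is relative over-recording in PM+. It is not certain: assessors ask participants not to discuss the services they receive, which could suppress some volunteered reports at the shared interviews.

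The size cannot be derived from the documents. A false ratio of about 1.4-1.5 rests on an assumed 10-20% detection chance per contact, uniform onset, sessions at weeks 2-6 and full attendance; at 70% per contact it is 1.03. The imbalance in scheduled contact ends at midline. The change is worth making because it is cheap and serious events are foreseeable in this population.

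**What to change.** At midline and endline, in both arms, have the blinded assessor ask the same short yes/no list of events since the last assessment, for example hospital admission, self-harm, violence and serious illness. Ask it after the outcome measures, and do not ask about services received. Base any between-arm summary of adverse events on these answers alone. Keep spontaneous and staff-observed reports for safety-committee oversight, tabulated separately by source and arm.

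The cost is a minute or two at two existing interviews. There is also a small added risk of unblinding, and placing the questions last does not remove it. The Masking section recognises that an assessor unblinded in one interview remains so for the rest of that ward, so with eight participants up to seven later interviews could be affected. Closed wording limits the risk, and the record of unblinding that the protocol already keeps would track it.

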### Dissemination

Findings from the c-RCT will be published through various channels. In Nepal the results will be disseminated to key stakeholders, including district, provincial, and national government, through Nepali and English reports and presentations. Internationally, the findings will be published in academic journals and reports to the research funder (Office of US Disaster Foreign Assistance/USAID) and disseminated through the Mental Health Innovation Network (www.mhinnovation.net). For authorship eligibility we will comply with guidelines of the International Committee of Medical Journal Editors. Also, additional attention will be given to recommendations for equitable representation of researchers from LMIC for academic authorship [62]. After publication of the primary analyses, the data will be made publicly available to keep with transparency recommendations.

## Discussion

The described c-RCT on the effectiveness of Group PM+ in Nepal has been informed by a preceding formative work and a feasibility c-RCT with Group PM+ in Nepal [10]. It will contribute to the building evidence base for transdiagnostic psychological interventions delivered by non-specialists for people in communities affected by adversity. It builds upon the results and shown effectiveness of individual PM+ in Kenya [11] and Pakistan [63] and the first RCT on the effectiveness of Group PM+ has been successfully completed in Swat valley in Pakistan [13].

After individual PM+ has been found to be effective in Kenya and Pakistan, it was released for use by the WHO [2]. The intervention manual is now used in different settings all over the world, increasing access to an evidence-based intervention for people with mental health problems. If Group PM+ is effective in both Pakistan and Nepal, the Group PM+ manual will also be published and available on WHO’s website for free. This will give opportunity for further adaptation and implementation of the intervention in diverse settings with communities that are in need of better access to psychological interventions. The intervention can be adapted for other LMIC and humanitarian settings, but also in high income settings where brief transdiagnostic group interventions are lacking.

### Trial status

The trial is open and recruiting as of November 25, 2018 and will likely be completed by May 31, 2019. The protocol (version 3) was last verified 25 October 2018. Subsequent protocol modifications will be reported to funders, IRBs, and registered with ClinicalTrials.gov.

## Data Availability

Data sharing is not applicable to this article as no datasets were generated or analyzed during the current study. See protocol manuscript for details on planned data sharing for data generated from planned study.

## Abbreviations

AE: Adverse event
AUDIT: Alcohol Use Disorder Identification Test
c-RCT: Cluster randomized controlled trial
CI: Community informant
CIDT: Community Informant Detection Tool
CMD: Common mental disorders
CPSW: Community psychosocial workers
DSMC: Data Safety Management Committee
ENACT: Enhancing Assessment of Common Therapeutic Factors
EUC: Enhanced usual care
FGD: Focus group discussion
GHQ: General Health Questionnaire
IRGT: Individually randomized group treatment trial
LMIC: Low- and middle-income countries
mhGAP: Mental health Gap Action Programme
ODK: Open data kit
PM+: Problem Management Plus
PHCCs: Primary health care centers
PHQ: Patient Health Questionnaire
PRIME: Programme for Improving Mental Health Care
PTSD: Posttraumatic stress disorder
SAE: Serious adverse event
TPO: Transcultural Psychosocial Organization Nepal
WHO: World Health Organization
WHODAS: World Health Organization Disability Assessment Scale
